### Description of Intervention

The CFP intervention includes two major components:

1) Patients receiving the intervention will undergo a CFP consultation assessment by a member of a multidisciplinary team of mental health providers (e.g., psychiatrists, psychologists) who are bilingual and/or bicultural, trained in culturally competent techniques, and familiar with the cultures and languages of the clients served. The Engagement Interview Protocol and DSM-IV-TR Cultural Formulation model will be utilized to make a culturally appropriate diagnosis, assess the patient's psychiatric needs in a cultural context, conduct a culturally focused intervention, engage the patient, and make recommendations to the PCP [15,20,21]. The CFP clinician will work collaboratively with the patient's PCP to communicate diagnostic and treatment recommendations after the two-week follow-up visit. Given the critical nature of communicating the CFP findings to the PCP, the CFP clinician will work with the PCP to determine his preferences for communication. Recommendations can be given to the PCP by multiple avenues: by e-mailed letter, and/or by page or phone call as needed. Clinicians will make themselves available to PCPs on an as-needed basis throughout the study period.

2) Patients will receive a culturally appropriate CFP consultation patient toolkit, available in their language of preference (i.e., English, Spanish, Chinese, or Vietnamese), as well as training in using the toolkit materials. The patient toolkit was added to enrich the intervention by providing patients with psychoeducation, handouts on managing depression based on cognitive behavioral therapy techniques, and information on community resources [22]. To help in the management of their depression, patients will be encouraged to complete these materials and bring them to visits with their PCP. In addition, within two weeks of the initial consultation, patients will attend a follow-up visit with the CFP clinician to review and answer their questions about the treatment of their depressive symptoms. The CFP clinician will also review patients' understanding of the toolkit, including their use of the cognitive-behavioral based handouts. To add flexibility in follow-up for patients, these visits can be done in person or over the phone.

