### Target Health Condition

All patients in the intervention and usual care (control) arms will be screened for clinical depression using the self-rated PHQ-2 at their primary care visit. Both patients and PCPs will be notified of positive screening results for all patients assessed. For the intervention arm, diagnoses of specific depressive disorders (major depressive disorder, dysthymia, depressive disorder NOS, adjustment disorder with depressed mood) will be established during the baseline clinical interview using DSM-IV-TR criteria [21].

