### Initial Screen

On the screening form, patients will be administered the PHQ-2 and asked additional questions about gender, age, race, ethnicity, and language spoken at home. Using a cutoff score of two or above (out of a possible total score of six), the PHQ-2 has been validated for diagnosing any clinical depressive disorder with a 82.1 percent sensitivity, 80.4 percent specificity, and a positive predictive value of 48.3 percent (assuming 18 percent prevalence of any depressive disorder) [23]; it consists of the first two questions of the PHQ-9, which has been translated into Chinese, Vietnamese, and Spanish [23-27]. The screening form will be available in multiple languages (English, Spanish, Chinese, and Vietnamese).

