### Six-month follow-up

Patients will have the option to complete the visit over the phone or in person. In both the intervention and usual care arms, patients will be given the QIDS-SR self-rated questionnaire and asked a brief "Resource Utilization Questionnaire" with questions regarding use of antidepressant medications, referrals/visits to mental health specialists, or alternative providers both in and out of the MGH system. The electronic medical record will also be reviewed at baseline and at the six-month follow-up for both intervention and usual care arms to obtain depression diagnoses, prescription of antidepressant medications, and referrals/visits to mental health specialists in the system.

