### Exploratory analysis

Descriptive analyses will be performed to provide information related to the study's experience conducting the initial screening patients within their primary care clinics.

Data from initial screens will be utilized to provide a greater description of the patient population at screening, recruitment and enrollment (e.g., race; ethnicity; preferred language; age; gender; level of depression (i.e., PHQ-2 score); service utilization, as well as identify which of these variables, if any, served to influence participation in the study. This information will allow us to describe, for example, whether consent to be contacted differs by level of depression and whether this is moderated by demographic factors (e.g., race, ethnicity, gender). Additionally we will provide additional data describing rates of enrollment as compared to the total screened.

Secondary exploratory analyses will explore the impact of the intervention on depression. Patients' scores on the QIDS-SR will be compared between the usual care and intervention arms. To measure changes in racial and ethnic disparities in depression recognition and treatment, rates of depression diagnoses will be compared from baseline to six-month follow-up for the intervention and usual care arms. As measures of the use of any ongoing specialty mental health care, the rates of prescription of pharmacotherapy and referrals/visits to mental health specialists as provided by patient self-report will be compared at baseline and at the six-month follow-up. Data analysis will be conducted using STATA statistical software [35].

A general linear model that accounts for clustering at the PCP level will be used. Analyses of the main outcomes will include as covariates any patient or physician factors that differed significantly between study arms. Outcomes regarding diagnosis and treatment will be assessed using general estimating equations with a binomial link and standard errors will be adjusted to account for clustering within practice. Separate analyses will be conducted for each outcome (i.e., dependent variables) -- changes in depressive symptoms, diagnosis of and treatment (prescription of antidepressant medications; referrals/visits to mental health specialists) for depression at six months after enrollment. The effect of study arm on each outcome will be assessed, controlling for significant differences emerging from the bivariate analyses.

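### The exploratory outcome on mental health specialist visits does not exclude the two study consultations, so the intervention arm can appear to gain specialist care when later care is unchanged

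*Protocol article*

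**What the plan says.** The Description of Intervention has each intervention patient assessed in a culturally focused psychiatric (CFP) consultation by "a member of a multidisciplinary team of mental health providers (e.g., psychiatrists, psychologists" being the examples given). It adds that "within two weeks of the initial consultation, patients will attend a follow-up visit with the CFP clinician". Usual-care patients are offered the intervention only at the end of the study (Definition of Usual Care).

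The Six-month follow-up section describes a Resource Utilization Questionnaire that asks about mental health specialists inside and outside the hospital system. It also describes a review of the electronic record in both arms "to obtain depression diagnoses, prescription of antidepressant medications, and referrals/visits to mental health specialists in the system". Under Exploratory analysis, "the rates of prescription of pharmacotherapy and referrals/visits to mental health specialists as provided by patient self-report will be compared" at baseline and six months. That sentence opens with the purpose: "As measures of the use of any ongoing specialty mental health care". The closing paragraph of the section lists referrals or visits to specialists again as a treatment outcome at six months, without the word 'ongoing'.

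No section says whether the CFP contacts count as specialist visits.

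**The concern.** Read literally, the outcome can count the assigned treatment as its own success. The CFP clinicians are mental health specialists in the ordinary sense. The second contact falls within two weeks of the first, so well inside the six-month period, and only one arm has these contacts during follow-up. Comparison with baseline does not help, because the contacts come after the baseline state that is being compared.

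The weakness lies in data collection as well as analysis. If the questionnaire item does not separate study visits from others, a 'yes' cannot later be attributed to one or the other. Chart review could separate them only for care inside the hospital system.

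At stake is a between-arm measure of whether the service leads patients into treatment. The Sample size and power section says that the exploratory results are to inform later versions of the intervention and design, and a spurious gap would mislead that step.

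**Working it through.** The article gives no figure for this outcome, so there is none to reproduce. The check asks what the comparison would show if the intervention changed nothing in later care.

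**Inputs**
- p, the share in either arm with a specialist visit other than the CFP contacts, set equal in both arms. Illustrative value: 9/38 = 24%, the patients referred to mental health services in the PCP-notification study described under Preliminary Studies. Adding the four with both a prescription and a referral gives 13/38 = 34%. A range of 10% to 50% is assumed.
- c, the share of the remaining intervention patients who report the CFP contact as a specialist visit. The documents give no value; 10%, 25% and 50% are assumed, with 100% as the limit.
- n = 120/2 = 60 per arm (Sample size and power).
- Two-sided 5% test, assumed; clustering ignored at first.

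**Formulas**
- Observed intervention rate: p₁ = p + (1 − p)c
- False difference: d = p₁ − p = (1 − p)c
- Chance of significance: Φ{[d − 1.96√(2p̄(1 − p̄)/n)] / √[p₁(1 − p₁)/n + p(1 − p)/n]}, with p̄ the mean of the two rates

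**Worked case, p = 24% and c = 25%**
- p₁ = 0.24 + 0.76 × 0.25 = 0.43; d = 0.19; p̄ = 0.335
- 1.96 × √(2 × 0.335 × 0.665/60) = 1.96 × 0.0862 = 0.169
- √(0.43 × 0.57/60 + 0.24 × 0.76/60) = 0.0844
- (0.190 − 0.169)/0.0844 = 0.25, and Φ(0.25) = 0.60

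**Results at 60 per arm**

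| c | p = 24%: false difference | chance significant | p = 34%: false difference | chance significant |
|---|---|---|---|---|
| 10% | 7.6 points | 15% | 6.6 points | 11% |
| 25% | 19 points | 60% | 16.5 points | 45% |
| 50% | 38 points | 99% | 33 points | 96% |
| 100% | 76 points | about 100% | 66 points | about 100% |

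Over p from 10% to 50%:
- c = 10%: 5 to 9 points, chance of significance 8% to 29%
- c = 25%: 12.5 to 22.5 points, 28% to 86%
- c = 50%: 25 to 45 points, 82% to 100%

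The plan's analysis allows for clustering, which lowers these chances but leaves the false difference unchanged. With an assumed design effect of 1.5 (60/1.5 = 40 effective patients per arm) and p = 24%, the chances for c = 10%, 25% and 50% are about 11%, 44% and 95%.

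If CFP contacts are excluded, c = 0, the difference is 0 and the rejection rate returns to the nominal 5%.

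**The case against.** The best defence is that the article nowhere says CFP contacts are counted. The word 'ongoing' points away from a two-contact consultation. Table 1 lists the consultation and the utilization questionnaire as separate rows, and consultation costs are treated separately from service use. The questionnaire items and chart-abstraction rules are not shown, and an article may leave such detail to the full protocol. All of this stands as a limit on certainty: a reader might infer that the intervention arm must come out ahead, and the documents do not support that. At c = 10% the bias is modest and seldom significant. But 'ongoing' appears once, as a statement of purpose, and is never turned into a rule. Where the outcome itself is described, it is plain referrals or visits.

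A reader might also infer that the diagnosis outcome is circular, because "For the intervention arm, diagnoses of specific depressive disorders" are made at the baseline interview and usual care has no study interview. The documents do not establish this. The stated source is the medical record in both arms, and the article does not say that the CFP diagnosis is entered there. A PCP who records depression after CFP advice is showing the recognition effect under study. The screen's stated predictive value ("a positive predictive value of 48.3 percent") does not rescue the inference: it assumes 18% prevalence among those screened, and an interview that rules depression out would lower the intervention arm's rate, not raise it.

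The same sentence covers prescriptions. No section has CFP clinicians prescribing; they make recommendations to the PCP. That outcome is not shown to be affected.

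**Conclusion.** The point holds for specialist visits: as published, the outcome is open to counting the intervention itself, in one direction and in one arm only. The size depends on how many patients report the consultation, which the documents do not give. At a 24% base rate the false difference runs from about 8 points (c = 10%) to 38 points (c = 50%); from about c = 25% upward it could well be declared significant at 60 per arm. These figures assume equal true later care, a base rate borrowed from a different study, and no clustering except where stated.

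The diagnosis outcome is at risk only if the CFP team's own entries reach the medical record. The prescription outcome and the primary aim (feasibility, satisfaction and cost) are not affected. The analyses are labelled secondary and exploratory, so no primary conclusion rests on them. The case for acting is that the bias is one-sided and almost free to remove.

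**What to change.** - In the Resource Utilization Questionnaire, add 'other than the study consultation' to the specialist-visit item.
- In Six-month follow-up and Exploratory analysis, state that CFP visits, and any diagnosis entered in the record by the CFP team itself, do not count as outcome events. Carry this into the chart-abstraction form.
- State in the same place what still counts: diagnoses, referrals and prescriptions made by the PCP after CFP advice, and visits to non-study specialists that follow a CFP recommendation. These are real effects of the service.

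There is no need to replace self-report with the medical record as the main source, to drop onward referrals prompted by the consultation, or to restrict the analysis to patients above a QIDS-SR threshold. Those steps are debatable or could remove genuine effects.

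The cost is one questionnaire phrase and one abstraction rule. The downside is that the apparent effect may be smaller. If six-month questionnaires have already been collected without the phrase, those answers should be reported with that limitation.

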## Methods/Design

### Overview

This is a randomized controlled trial of the CFP intervention. During the study period, all patients in participating primary care clinics will receive a screening form for symptoms of depression; data on age, gender, race, ethnicity and primary language will be obtained at the time of screening. Asian American and Latino American patients who screen positive for clinical depression will be contacted by study staff and invited to participate in the CFP study. Eligible patients will be randomized either to the intervention arm or usual care based on their primary care provider. Patients in the intervention arm will receive the CFP intervention over two visits and then called at six-months by study staff to administer follow-up questionnaires (described below). Patients in the usual care arm will be called at baseline and at six-month follow-up by study staff to administer questionnaires (described below). To evaluate the cultural components of the study, a number of qualitative interviews will also be conducted with participants in the intervention and usual care arms, and with members of the target population who did not participate in the study. Please see Figure 1 for the study flowchart.

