### Target PCP practices

The intervention will be conducted at four MGH primary care practices; each PCP practice consists of multiple sub-practices called pods.

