### Randomization scheme

Primary care patients at MGH will be randomized by pods, which comprise multiple clusters of 5-6 PCPs within each practice site. Using electronic medical records data from 2007, practices will be matched based on an index composed of two variables: 1) the number of patients who are members of the target minority groups and 2) the rate of diagnosed depression. Within each pair, one practice will be randomized to participate in the intervention and the other will be assigned to the "usual care" arm.

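### The randomised unit is stated two ways, pod and practice, and the exploratory effect models cluster by PCP and by practice, so neither is tied to a settled unit

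*Protocol article*

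**What the plan says.** All references are to the protocol article.

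- **Randomization scheme**, opening sentence: "Primary care patients at MGH will be randomized by pods, which comprise multiple clusters of 5-6 PCPs within each practice site". On any reading, a pod holds several PCPs.
- The same section then says that practices are matched on an index of target-minority patient numbers and rate of diagnosed depression, and continues: "Within each pair, one practice will be randomized to participate in the intervention".
- **Target PCP practices**: "The intervention will be conducted at four MGH primary care practices", each made up of several pods. The number of pods is not given.
- **Overview**: "Eligible patients will be randomized either to the intervention arm or usual care based on their primary care provider".
- **Exploratory analysis**, linear model: "A general linear model that accounts for clustering at the PCP level will be used".
- The same section, GEE for diagnosis and treatment: "standard errors will be adjusted to account for clustering within practice".

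The effect comparisons are labelled secondary exploratory. Under Study Aims, the primary aim is feasibility, satisfaction and cost.

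**The concern.** In a cluster-randomised comparison, the standard error has to reflect variation between the units that were randomised. Here that unit is not settled, because pod and practice cannot both be the unit. The two model families also use different clustering levels, with no reason given, and neither uses the pod.

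The two models raise different problems. The linear model clusters below either candidate unit, so it treats PCPs in the same randomised pod or practice as independent. The GEE clusters at or above either candidate unit, so its level is not too low, but it has only four clusters on which to estimate a variance.

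At stake are the between-arm confidence intervals and p-values for QIDS-SR, depression diagnosis, antidepressant prescription and specialist referrals or visits. The section on sample size and power says that the exploratory results will inform later versions of the intervention and study design, so intervals that are too narrow could mislead those decisions.

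**Working it through.** **Inputs from the article.** Four practices; several pods per practice; 120 patients split evenly between arms (Sample size and power); the clustering levels quoted above. No intraclass correlation, design effect, number of pods or small-sample method is given, so there is no figure of the plan's own to reproduce.

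**Assumptions.** 30 patients per practice (120/4); 2 or 4 pods per practice; 5 PCPs per pod. This gives 15 or 7.5 patients per pod and 3 or 1.5 per PCP. Practice, pod and PCP shares of total variance each lie between 0 and 0.05.

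**Step 1: PCP-level clustering in closed form.** Let *m* be patients per unit and ρ the variance share at each level. The variance inflation that a PCP-level robust standard error picks up is approximately

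D_used = 1 + (m_PCP − 1)(ρ_PCP + ρ_pod + ρ_prac).

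The inflation that applies is

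D_true = 1 + (m_PCP − 1)ρ_PCP + (m_pod − 1)ρ_pod + (m_prac − 1)ρ_prac,

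where the practice term counts only if practices are randomised. The actual size of the test is P(|Z| > 1.96/√(D_true/D_used)).

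- Pods randomised, 2 per practice, ρ_PCP = 0.02, ρ_pod = 0.05, ρ_prac = 0: D_used = 1 + 2(0.07) = 1.14; D_true = 1 + 2(0.02) + 14(0.05) = 1.74; ratio 1.53; P(|Z| > 1.59) ≈ 11%.
- The same with ρ_pod = 0.01: 1.06 against 1.18; ratio 1.11; P(|Z| > 1.86) ≈ 6%.
- Practices randomised, ρ_PCP = ρ_pod = 0.02, ρ_prac = 0.05: D_used = 1 + 2(0.09) = 1.18; D_true = 1 + 2(0.02) + 14(0.02) + 29(0.05) = 2.77; ratio 2.35; P(|Z| > 1.28) ≈ 20%.

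**Step 2: practice-level clustering in closed form.**

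- Practices randomised, two per arm: the uncorrected sandwich variance is on average half the unbiased one, so the size is P(|t₂| > 1.96/√2) = 30%.
- Pods randomised, both arms in every practice: P(|t₃| > 1.96√(3/4)) = 19%.
- With a G/(G − 1) = 4/3 correction and the t₃ critical value of 3.182: P(|t₂| > 3.182√(2/3)) = 12% and P(|t₃| > 3.182) = 5%.

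**Step 3: simulation under no effect.** 2,500 runs per setting, continuous outcome, independence working correlation. Monte Carlo standard error near 5% is √(0.05 × 0.95/2500) = 0.4 percentage points.

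| Standard error and reference | Pods randomised | Practices randomised |
|---|---|---|
| By PCP (linear model as written) | 4.6-12.3% | 4.2-25.0% |
| By practice, uncorrected z | 17-21% | 29-36% |
| By practice, G/(G − 1) correction, z | 13-17% | 25-31% |
| By practice, t on 3 df | 4-7% | 12-15% |
| By pod, t on G − 1 df | 3.3-7.2% | 5.9-18.6% |

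In the first row with pods randomised, the size is about 5-6% at pod shares of 0-0.01, 6-8% at 0.02 and 8-12% at 0.05. With practices randomised, it is about 10% at a practice share of 0.01, 14% at 0.02 and 22-25% at 0.05. The simulation agrees with the closed forms.

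**Step 4: practices as the unit.** Four practices make two matched pairs and 2² = 4 possible allocations. Each allocation and its mirror image give the same absolute difference, so the smallest two-sided randomisation p-value is 2/4 = 0.5. This needs no assumed variance share.

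**The case against.** A reader might infer that both clustering choices make standard errors too small and that false-positive rates far exceed 5%. The documents do not support that.

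- **The level is wrong only for the linear model.** Practice is at or above either candidate unit, so practice clustering does not omit between-unit correlation. The weakness there is four clusters.
- **The PCP-level inflation is conditional.** It depends on variance shares and a number of pods that the article does not give. It is absent if pods and practices do not vary, modest if pods are randomised, and large mainly if practices are randomised with a practice share of about 0.02 or more.
- **The uncorrected z-test is not in the plan.** The article does not say which variance estimator or reference distribution the GEE will use, and it may leave this to a fuller document. With t on 3 df and pods randomised, practice clustering is roughly valid.
- **The Overview sentence need not be a third unit.** A patient's arm can follow the PCP because the PCP belongs to an allocated pod or practice.
- **Loose wording is possible.** The article calls pods sub-practices, so practice may sometimes mean pod.
- **The comparisons are exploratory**, and the Discussion leaves evidence of effectiveness to a later, larger trial.

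All of this stands, and it limits the size and weight of the point. It does not remove it. Loose use of practice would not rescue clustering by PCP, which lies below both candidates. Stating a level below the randomised unit is a wrong rule on the page, not a detail left out.

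**Conclusion.** The point holds in limited form and should be fixed. Two conclusions rest on the text alone: the Randomization scheme gives two incompatible units, and the linear model clusters below both. If the four practices were randomised, no randomisation test at the 5% level is possible, again without further assumption.

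The sizes are conditional on the layout and variance shares assumed above: about 5-12% (pods) or 4-25% (practices) for the PCP-level model, and the four-cluster figures in the table for the GEE. The GEE figures come from a continuous outcome with an identity link, whereas the planned outcomes are binary, so they are approximate. The consequence is confined to the exploratory between-arm analyses.

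**What to change.** 1. In the Overview and the Randomization scheme, state the one unit that was actually randomised and the unit that was matched. Recruitment has begun, so this is a fact to report. It should not be presumed to be the pod: the matching sentence speaks of practices, and pod-level clustering would itself be too low if practices were randomised (last row of the table).
2. In the Exploratory analysis, replace both clustering levels with that unit, in the linear model and in the GEE alike, and use a small-sample-corrected variance with a t reference.
3. If pods were randomised, include the matching pair or the practice as a factor. Pod clustering with t on G − 1 df then held the simulated size at 3.3-7.2%.
4. If the four practices were randomised, report between-arm estimates descriptively and do not apply a 5% test.

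The cost is a change of wording and of cluster identifier, and wider confidence intervals. No new data are needed.

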### Analytic Plan

*Description of Measures *(See Table 1):

**Table 1 T1:** Patient measures administered over study period.

PATIENT MEASURES BY TIMEPOINT					
	**Screen**	**Baseline Assessment**	**2 Week Follow-Up^+^**	**6 Month Follow-Up^+^**	**Qualitative Interview^+^**

MINI International Neuropsychiatric Interview (MINI)*		X			

Quick Inventory of Depressive Symptomatology (QIDS-SR)		X		X	

Resource Utilization Questionnaire		X		X	

CFP Consultation, Assessment & Toolkit*		X	X		

Global Assessment of Functioning (GAF)*		X			

Patient Health Questionnaire (PHQ-2)	X				

Patient Satisfaction Questionnaire				X	

Schwartz Outcome Scale (SOS-10)		X	X	X	

Demographic Questionnaire		X			

Qualitative interview					X

*Intervention arm only.

^+ ^Visit may be conducted by phone.

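### Covariates are picked by significance tests of arm differences, so baseline QIDS-SR, though collected in both arms, has no assured place in the depression model

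*Protocol article*

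**What the plan says.** The Exploratory analysis section of the protocol article states the covariate rule twice. First: "Analyses of the main outcomes will include as covariates any patient or physician factors that differed significantly between study arms". Then, at the end of the section: "The effect of study arm on each outcome will be assessed, controlling for significant differences emerging from the bivariate analyses". No covariate is named in advance and no significance level is given for the selection.

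On the outcome, the section first says "Patients' scores on the QIDS-SR will be compared between the usual care and intervention arms", and later lists the dependent variables as "changes in depressive symptoms, diagnosis of and treatment" at six months. The model is described only as follows: "A general linear model that accounts for clustering at the PCP level will be used". Baseline QIDS-SR is not named as a term.

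Baseline QIDS-SR is available. Table 1 lists it at baseline without the mark for intervention-only measures, and the Baseline Visit section includes it for usual care. The section labels the depression comparison as secondary exploratory. The primary aim (Study Aims) is feasibility, satisfaction and cost.

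**The concern.** Whether a factor differs significantly between arms depends on chance and sample size. It does not show whether the factor predicts outcome. A rule built on such tests can leave out the baseline value of the outcome, usually the obvious prognostic covariate, and admit factors with no bearing on outcome. If the dependent variable is a change score and baseline is left out, a baseline difference too small to be significant still distorts the arm comparison through regression to the mean.

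What is at stake is the precision and interpretability of the QIDS-SR estimate. Sample size and power reports a cut from 506 to 120 patients and says the exploratory results will inform further versions of the intervention and design. The Discussion looks ahead to a large-scale trial. Avoidable noise in the estimate therefore matters, even though no confirmatory claim rests on it.

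**Working it through.** The article gives no figure for this rule, so there is none to reproduce. From the article: 120 patients, 60 per arm. Assumed: two-sided 5% tests, equal SD at baseline and six months, correlation r between them, independent patients. The article states neither r nor an ICC.

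**1. How often would baseline QIDS-SR enter?** If imbalance is due to chance alone, a 5% test admits it in about 5% of trials (4.6% to 5.5% in simulation). It is left out about 95% of the time.

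**2. Variance of the arm contrast, in units of the six-month variance.**
- Change score: 2(1−r).
- Baseline-adjusted (ANCOVA): 1−r².
- Ratio ANCOVA/change: (1−r²)/[2(1−r)] = (1+r)/2.
- Detectable difference at 80% power with 60 per arm and no design effect: (1.96+0.84)·√(2V/60), where V is the variance above.

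| r | Change | ANCOVA | Ratio | Detectable, change (SD) | Detectable, ANCOVA (SD) |
|---|---|---|---|---|---|
| 0.3 | 1.40 | 0.91 | 0.65 | 0.61 | 0.49 |
| 0.5 | 1.00 | 0.75 | 0.75 | 0.51 | 0.44 |
| 0.6 | 0.80 | 0.64 | 0.80 | 0.46 | 0.41 |

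If unadjusted six-month scores were meant, the ratio is 1−r²: 0.91, 0.75 and 0.64. Precision is lost on either reading.

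**3. Simulated power and error.** There were 60 per arm, 8,000 runs per scenario, a true effect of 0.5 SD or zero, and no clustering. The rule was applied to baseline QIDS-SR only.

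| r | Power: change, no covariate | Power: change with the rule | Power: ANCOVA always | Null rejection: change with the rule | Null rejection: ANCOVA |
|---|---|---|---|---|---|
| 0.3 | 62% | 64% | 81% | 4.1% | 5.0% |
| 0.5 | 77% | 78% | 87% | 4.5% | 5.2% |
| 0.7 | 94% | 94% | 97% | 4.5% | 4.8% |

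The rule recovers almost none of the available precision, and it is slightly conservative. Applied to the six-month score instead, it rejects 3.7% to 4.7% at the null. With ten candidate factors including baseline, applied to change, a repeat gave 4.0%, 4.0% and 4.7%.

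**4. An imbalance the rule would miss (illustration).** A 0.3 SD baseline difference gives z = 0.3/√(2/60) = 0.3×√30 = 1.64, p = 0.10, so baseline stays out. Given that imbalance, the change-score contrast is off by (1−r)×0.3 = 0.15 SD at r = 0.5. An unadjusted six-month contrast would be off by r×0.3, also 0.15 SD.

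**5. Factors admitted by chance.** With k independent tests at 5%, the chance that at least one is selected is 1−0.95^k: 23% for k = 5 and 40% for k = 10. The number of candidates is not in the article.

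**The case against.** **The comparison is exploratory.** It is labelled so, and the primary aim lies elsewhere. The wording about main outcomes in the covariate sentence is loose and does not make QIDS-SR primary. This stands and lowers the priority.

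**The article does not bar baseline QIDS-SR.** The rule says what will be included, and a condensed article may leave model terms to a fuller plan. It also speaks of both scores and changes. This stands in part: a reader might infer that the plan definitely omits baseline, and the text does not go that far. But the selection rule is an explicit choice, made twice, and on its terms baseline has no assured place.

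**Error rates.** A reader might infer that data-driven selection inflates false positives. The simulations do not support that.

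**Sample-size equivalence.** A reader might convert the ratio into 120 patients acting like 120/0.80 = 150 to 120/0.65 = 185. That treats patients as independent, whereas the trial randomises clusters (Randomization scheme), and r is assumed. The conversion should not be used.

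**Invalid baseline tests.** A reader might also infer that the bivariate tests ignore clustering. The article does not say whether they do.

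**Imbalance may be systematic.** Patients consent at the baseline visit under provider-based allocation, and bipolar disorder is excluded only in the intervention arm. The chance-only figures in steps 1 and 5 may therefore not describe this trial, and adjustment has a real purpose. That argues for adjusting on factors chosen for prognosis. It does not argue for choosing them by p-value.

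**Conclusion.** The point holds as a moderate-to-minor one. The stated rule makes the model depend on the data and, taken literally, leaves baseline QIDS-SR out unless it differs significantly. The consequences are lost precision, uncorrected imbalance and an adjustment set unknown in advance.

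At the individual level, with equal SDs and r of 0.3 to 0.6, always adjusting for baseline brings the variance to 0.65 to 0.80 of that of a change score. Some gain exists for any r below 1 under these assumptions, but clustering may alter its size. The 0.15 SD distortion is conditional on a chosen imbalance and is not an expected bias. The 40% figure rests on ten independent tests at 5%, both assumed.

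**What to change.** - Delete both significance-based covariate rules in the Exploratory analysis section.
- State one model for depression: six-month QIDS-SR on arm, baseline QIDS-SR (always included) and a short list fixed in advance for prognostic value, for example ethnic group, age and sex. Keeping change as the outcome with baseline QIDS-SR as a covariate gives the same arm estimate in a linear model, so the baseline term is what matters.
- Account for clustering at the randomised unit. The Randomization scheme section refers to both pods and practices, so the text must say which unit it is.
- Add the matching pair only as far as the number of clusters allows. Target PCP practices lists four practices, so the covariate list must stay short. If practices are the randomised unit, do not add a practice term, because it is confounded with arm.
- For diagnosis and treatment outcomes, adjust for the baseline value of the same outcome where it exists in both arms. The record review described under Six-month follow-up covers both arms at baseline.

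The cost is wording and a few degrees of freedom; baseline QIDS-SR needs no new collection. The primary model also loses the data-driven response to unexpected patient or physician imbalance. That can be shown as a sensitivity analysis.
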